## Abstract

**Background:**

Emotional disorders such as depression and anxiety disorders share substantial similarities in their etiology and treatment. In recent decades, these commonalities have been increasingly recognized in classification systems and treatment programs crossing diagnostic boundaries.

**Methods:**

To examine the prospective effects of different transdiagnostic markers on relevant treatment outcomes, we plan to track a minimum of *N* = 200 patients with emotional disorders during their routine course of cognitive behavioral therapy at two German outpatient clinics. We will collect a wide range of transdiagnostic markers, ranging from basic perceptual processes and self-report measures to complex behavioral and neurobiological indicators, before entering therapy. Symptoms and psychopathological processes will be recorded before entering therapy, between the 20th and 24th therapy session, and at the end of therapy.

**Discussion:**

Our results could help to identify transdiagnostic markers with high predictive power, but also provide deeper insights into which patient groups with which symptom clusters are less likely to benefit from therapy, and for what reasons.

**Trial Registration:**

The trial was preregistered at the German Clinical Trial Register (DRKS-ID: DRKS00031206; 2023–05-09).

## Background

Rather than separate processes being responsible for the onset and maintenance of individual disorders, common transdiagnostic markers and processes linked to multiple mental disorders have been identified on the cognitive-emotional and biological level [1]. This is reflected in the development of alternative classification systems such as the Research Domain Criteria (RDoC) [2] or Hierarchical Taxonomy of Psychopathology (HiTOP) [3], and overarching disorder concepts [4]. For instance,’emotional disorders‘ describe a concept under which different disorders (e.g., anxiety disorders, unipolar depression) are grouped based on shared mechanisms contributing to their onset and maintenance [5]. Based on these conceptualizations, transdiagnostic psychotherapeutic interventions have been developed that incorporate these transdiagnostic mechanisms within treatment programs [4, 6]. However, studies investigating the relative influence and predictive power of a wide range of transdiagnostic factors over time within a naturalistic outpatient setting are lacking. In the TransTAM study, we aim to fill this gap by predicting symptom reduction using selected transdiagnostic factors covering most RDoC domains and units of analysis that have been identified as particularly relevant in the respective research areas. In the following paragraphs, we briefly introduce the most important factors (for additional constructs, see Table 2).

### Perceptual, cognitive and motor variability

Continuous psychophysics [7] is a recent methodological advance that overcomes the rigid structure of classical psychophysics tasks, which typically involve hundreds of trials with binary decisions. Instead, subjects make continuous behavioral adjustments in response to dynamically changing stimuli [8], e.g., by tracking moving targets with a computer mouse [7], their finger [9], or gaze [10]. Such tasks are not only more natural and less tedious for the subjects, but they enable us to characterize properties of the perception–action loop beyond perceptual sensitivity (e.g., numerosity, speed, and contrast) using just a few minutes of data. A recently developed computational modeling framework for continuous psychophysics based on inverse optimal control [11] allows us to infer subjects' motor variability, internal behavioral costs, and subjective beliefs about the stimulus dynamics in a theory-driven fashion. Such quantities have been linked to anxiety and affective disorders: For example, anxiety is related to differences in perceptual sensitivity to discriminating fearful and neutral faces [12, 13]. State anxiety is associated with reduced motor variability, marked by more repetitive and rigid movements [14, 15]. In terms of behavioral costs, the subjective cost of physical effort is higher for patients with major depressive disorder compared to healthy individuals [16, 17]. Despite these clinically relevant findings, less is known about the transdiagnostic relevance of these processes as well as their importance in predicting psychotherapeutic treatment outcome.

### Active vision

The free viewing of natural scenes yields rich data at minimum demand to the observer. It provides insight into general cognitive factors and mechanisms of potential transdiagnostic relevance, such as the individual tendency for visual exploration and social salience [18–20]. Recent research has shown that basic aspects of visual exploration behavior, like saccadic frequency and amplitudes, are diminished under acute fear [21] and in patients with affective disorders [22–25]. Moreover, social anxiety can lead to the visual avoidance of socially significant stimuli like faces and eyes [26]. Finally, affective disorders have been shown to accompany increased reaction times and slower saccadic velocity in pro- and anti-saccade tasks [25, 27]. Despite the high diagnostic potential of active vision, studies investigating its transdiagnostic and prognostic relevance remain scarce.

### Social contextual cues

Social context (e.g., facing a communication partner or seeing a speaker from a lateral perspective) plays a crucial role in communication and mental health, shaping the interpretation and response to language and social cues [28–31]. In mental disorders such as major depressive disorder [32], social anxiety disorder [33, 34], or schizophrenia [35], the ability to accurately interpret and respond to social contextual cues can be impaired, leading to difficulties in social communication and stronger feelings of isolation. Investigating these social factors in a transdiagnostic sample will help to understand the challenges faced by individuals with mental health conditions such as major depressive disorder and anxiety disorders, and highlights the need for interventions that enhance social functioning and reduce misinterpretations in social contexts [36]. The processing of social contextual information while communicating can be investigated by manipulating contextual factors such as gestures and body orientation in video clips [32]. For example, Suffel et al. [32] found that patients with major depressive disorder required increased neural effort, particularly in regions like the left inferior frontal gyrus and anterior cingulate gyrus, to interpret social contextual cues, which may contribute to their social difficulties. Whether the processing of socially relevant contextual cues is of transdiagnostic importance and a relevant predictor of symptom reduction in response to psychotherapy remains unknown.

### Social decision-making

Patients with depressive or anxiety disorders reveal marked distortions in social decision-making during social exchanges. These distortions relate to transdiagnostically relevant problems, such as the lack of reciprocity, social avoidance and mistrust, lack of perspective taking, insensitivity to social rewards, distorted social perception, interpersonal rumination, and pessimistic social expectations (for reviews, see [37–41]). Socioeconomic games such as trust games can be used to examine social decision-making across mental disorders and for behavioral phenotyping [42–44]. Unfortunately, little is known about whether and how patients’ biases in social decision-making during trust games (or other socioeconomic games) predict symptom reduction and other relevant treatment outcomes. It is also unclear whether these biases can be used as transdiagnostic markers of psychopathology in social symptom domains.

### Defensive reactivity

Various emotional disorders have been linked to abnormalities in the processing of and response to bodily sensations [45], which can manifest as dysfunctional defensive mobilization at both neural and behavioral levels [46–49]. Overexpressed defensive mobilization, which is clinically characterized by maladaptive anxiety, fear, and related behavioral changes such as avoidance, is transdiagnostically relevant and constitutes a core feature of several mental disorders [50]. Specifically, anxiety and fear of bodily sensations are known to be closely related to the development, persistence, and treatment-related amelioration of psychopathology [51–53]. To specifically probe potential dysfunctions of defensive circuits in the brain tied to somatic symptoms, previous studies have used interoceptive challenges to induce interoceptive perturbations (e.g., cardiorespiratory symptoms via hyperventilation) [54–57]. Initial evidence from studies with individuals who fear body symptoms revealed a pattern of increased defensive mobilization while anticipating and confronting interoceptive perturbations via hyperventilation [56, 58]. In particular, in patients with panic disorder, defensive mobilization toward interoceptive perturbations co-varied with disorder-specific symptom dimensions [59] and persisted in those patients whose symptoms failed to resolve enough after cognitive behavioral therapy (CBT) [46]. However, existing data on defensive mobilization to somatic symptoms are limited to specific mental disorders as classified by current classification systems of mental disorders (e.g., panic disorder). Our understanding of transdiagnostic processes related to aberrant defensive responding to somatic sensations and their underlying pathophysiological mechanisms is thus limited so far, especially in relation to treatment response.

### Pattern separation

Pattern separation is a hippocampus-dependent mnemonic process that enables the discrimination of similar experiences by forming distinct representations of stimulus features (memory encoding) which are later retrievable from memory [60–62]. Pattern separation extracts the difference in an input stimulus (e.g., today’s parking space) with already stored stimuli (yesterday’s parking space in the same garage) despite overlapping or similar features between the stimuli [63]. Impaired pattern separation is discussed as a risk or maintenance factor for emotional disorders and anxiety disorders in particular [64, 65] because it impacts how individuals process, encode and store information from their surroundings. Pattern separation is associated with fear conditioning and fear overgeneralization [66–68], etiologically relevant processes for emotional disorders [69–71]. The mnemonic similarity task (MST) [72] is used as a measure to assess behavioral pattern separation ability. Bernstein et al. [73] report reduced performance in pattern separation but not general recognition memory in patients with posttraumatic stress disorder and other mental disorders. There is also some evidence that individuals with higher levels of depression are worse at separating patterns than those with lower levels of depression [74], but opposite effects were reported in the discrimination of negative stimuli [75]. These findings emphasize the transdiagnostic relevance of behavioral pattern separation, but we still do not know if it also predicts response to psychotherapy.

### Fear conditioning and generalization

Structural and functional abnormalities in the hippocampus are known to be associated with emotional disorders (e.g., anxiety-related and depressive disorders) [76, 77]. The hippocampus is a key structure in regulating the context-dependent modulation of conditioned fear, e.g., extinction recall in a safe extinction context, as well as the renewal of conditioned fear in a novel and potentially dangerous context [78–80]. Moreover, previous research indicates altered context-dependent extinction recall (e.g., reduced activation of the ventromedial prefrontal cortex) in subjects with PTSD and several anxiety disorders [81–83]. A further relevant mechanism in emotional disorders is fear generalization, namely the transfer of a conditioned fear response to stimuli sharing similarity with a conditioned cue (CS) [84]. If a stimulus resembles the CS + (conditioned cue previously paired with the aversive consequence [unconditioned stimulus]), the hippocampus is thought to initiate a fear response by activating fear-expressing brain regions as in the amygdala [85]. Fear generalization is also of potential transdiagnostic relevance and thereby probably contributes to the development and maintenance of anxiety and stress-related disorders [86–88]. Moreover, there is initial evidence that fear conditioning and generalization are associated with therapy outcome [89–91]. However, previous research leaves open the question whether context-dependent fear conditioning and generalization are related to transdiagnostic symptom dimensions in emotional disorders and can predict CBT-related symptom reduction.

### Emotional facial expression processing

The Hariri Task, also known as the emotional faces task, is a functional magnetic resonance imaging (fMRI) task used to study brain responses to emotional stimuli [92, 93]. Participants view faces expressing strong emotions (like fear or anger) and neutral objects (like shapes or spheres) and are asked to identify if the left or right stimulus is identical to the central one. This task has served to investigate amygdala functioning in conditions like depression and anxiety, where emotional regulation may be impaired. The emotional face-matching task used in fMRI studies has been explored further for its potential to predict treatment outcomes. However, recent research suggests caution in overestimating the predictive capabilities of fMRI, including tasks like the Hariri Task [94]. However, as of now, the predictive power of the Hariri Task and similar fMRI tasks for treatment outcomes remains an ongoing research and development area. The frequent use of the Hariri Task helps to connect findings to other cohorts (e.g., [93]) and to share data efficiently. New analyses approaches with the face-matching task considering for example the repetition of stimuli, neural variability (e.g., [95]) or different emotions (fear vs. anger; e.g., [96]) are promising new avenues to make these tasks more reliable and increase their predictive power in a transdiagnostic sample.

### Emotion regulation

Cognitive restructuring of mental distortions, e.g., via cognitive reappraisal, supposedly plays a crucial role in CBT [97, 98], the gold standard intervention for mental disorders [99, 100]. Thereby, cognitive reappraisal has shown to be impaired across mental disorders as indicated by deviant brain activation during reappraisal when compared to healthy controls (for a meta-analysis see [101, 102]). Recent findings show that especially those brain regions involved in cognitive and emotional processing such as the dorsomedial prefrontal cortex or anterior cingulate cortex predict CBT outcome across different emotional paradigms in anxiety-related disorders [103]. Regarding emotional reactivity and reappraisal, this was established for PTSD [104, 105], social anxiety disorder [106–108], and panic disorder [109, 110]. Similar regions were also identified for predicting therapy response in depression during emotion regulation [111]. Furthermore, brain activation during reappraisal (vs. looking at aversive pictures) outperformed the prediction of therapy response in social anxiety disorder compared to demographic data or symptom severity before treatment [108]. Despite its high transdiagnostic relevance, no study has investigated the prediction of therapy response during cognitive reappraisal in a mixed patient sample suffering from emotional disorders.

### Brain structural connectivity

Structural connectivity anomalies are a consistent finding in patients with unipolar or bipolar depression and anxiety-related disorders (e.g., [112, 113]). Specific transdiagnostic relationships between altered circuits (e.g., for amygdala structural connectivity) have been described. Evidence of alterations in the amygdala’s structural connectivity as visualized in Diffusion Tensor Imaging (DTI) have also been related to the prediction of treatment response [114]. Moreover, inflammation biomarkers such as cytokines are reliably elevated in a subset of patients with unipolar or bipolar depression and anxiety-related disorders, and have been associated with differential treatment responses and poor clinical outcomes. A growing body of literature also describes higher levels of endogenous inflammatory markers and altered, typically lower functional or structural connectivity within these circuits in association with transdiagnostic symptoms such as anhedonia and anxiety in psychiatric populations [115]. Interestingly, findings across neuroimaging modalities have consistently shown that the exogenous administration of cytokines or inflammatory stimuli that induce cytokines disrupts circuits and networks involved in threat detection, anxiety, and interoceptive and emotional processing [115]. Free-water imaging is a model-based approach [116, 117] that augments the DTI model by including a second compartment that accounts for the contribution of free-water throughout the brain; Free-water imaging allows us to disentangle two separate pathologies: one affecting the cellular domain such as axonal degeneration, and a second, more extensive pathology affecting the extracellular domain, potentially neuroinflammation. We recently demonstrated in a pilot study of patients with major depressive disorder [118] increased peripheral inflammatory markers (IL-8/ IL-10 ratio), as well as a positive correlation between the inflammatory profile and average free-water values. Moreover, responders to ketamine treatment showed higher baseline Fractional Anisotropy (FA) in the cellular/tissue compartment of the left cingulum bundle. It is important to mention that with advances in the acquisition of DTI data (multi-band, multi-shell approach) two compartment analyses have been substantially improved and the free water imaging-model fit becomes more robust [119].

### Brain functional connectivity

Resting-state fMRI (rs-fMRI) has become a valuable tool in neuroscience for studying the brain's functional organization, especially in populations that may have trouble performing tasks, ie, infants, elderly individuals, or patients with mental disorders. It offers potential insights into the underlying maladaptive mechanisms of these disorders and opens avenues for developing new diagnostic and therapeutic strategies. For example, patients with major depressive disorder exhibit altered brain dynamics compared to healthy controls, characterized by higher fractional occupancy and temporal stability in specific brain states, particularly one with weaker connectivity within and between all brain networks but higher activity in somatosensory, salience, and attention networks [120]. Research in major depression has also shown that individualized fMRI connectivity patterns before treatment can define signatures of antidepressant and placebo responses [121], the TMS response [122], or ECT response [123]. This suggests that rs-fMRI might help in identifying which patients will likely benefit from specific antidepressant treatments, thus paving the way for more personalized treatment approaches in major depression. Furthermore, resting state neuroimaging data proved to be informative in earlier studies for predictive models in social anxiety disorders with 81% accuracy, 84% sensitivity and 78% specificity [124]. However, rs-fMRI in a more recent study was not a significant predictor of CBT outcome in two large multi-site samples [125], suggesting that a combined analyses in context of other functional assessments in a transdiagnostic sample (with patients with anxiety disorders and depression) is an important avenue to understand the predictive value of relevant features from rs-fMRI. Further research is needed to refine these predictive models and validate their effectiveness in clinical practice.

### Objectives

The abovementioned transdiagnostic factors and processes have so far usually been investigated separately, if at all, or regarding specific disorders. The TransTAM study therefore aims to include and investigate a broad range of transdiagnostic mechanisms potentially relevant for predicting symptom reduction integratively in a mixed patient sample with emotional disorders (anxiety (-related) and depressive disorders) undergoing CBT in a routine outpatient setting. The main objectives of the TransTAM study are to investigate (1) the association between transdiagnostic symptom dimensions and transdiagnostic factors and mechanisms, and (2) the prediction of symptom reduction from various transdiagnostic processes (and their relative importance) across emotional disorders. Due to the broad scope of the measures included in the TransTAM study, a variety of research questions and hypotheses will be investigated. Examples for research questions are listed below:Are transdiagnostic symptom dimensions related to subjective and physiological correlates of defensive mobilization while anticipating and confronting hyperventilation-induced body symptoms?To what extent do indices of social decision behavior during social exchanges (e.g., cooperative behavior, recognizing changes in the social context) predict treatment response in terms of reducing symptom severity and interpersonal problems?

## Methods

### Study design and procedure

This bi-centric prospective-longitudinal observational study is investigating adult patients with emotional disorders receiving routine CBT treatment in one of the two outpatient units of the universities of Giessen and Marburg, Germany. During the probatory phase preceding psychotherapeutic treatment, patients are asked to participate in the TransTAM project if they report having psychological problems related to the disorders specified below and fulfill no exclusion criteria (see below). Structured diagnostic interviews [126–128] will be conducted during routine diagnostics within the probatory phase, and might subsequently lead to the exclusion of participants if any exclusion criteria are fulfilled, for example. Depending on specific exclusion criteria, patients can participate in different study parts: study part 1 (behavioral tasks and questionnaires), study part 2 (peripheral physiological experiment), and study part 3 (MRI measures and experiments). See Table 1 for our inclusion and exclusion criteria.

**Table 1 Tab1:** Inclusion and exclusion criteria

Inclusion criteria for all participants
1. Currently fulfilling the diagnostic criteria for a diagnosis in sections F32—F39 or F4 of ICD-10
2. Currently seeking cognitive-behavioral psychotherapeutic treatment in one of our two outpatient clinics
3. Therapy duration of at least 12 sessions or a regular end of therapy before 12 therapy sessions must be reached
4. Willingness to participate in the study
Exclusion criteria for all participants
1. Diagnosis from section F2 (according to ICD-10; e. g. schizophrenia)
2. Acute manic/hypomanic episode (diagnosis from domains F30 and F31 according to ICD-10)
3. Acute suicidality
4. Psychotic symptoms (e. g. during a major depressive episode)
5. Organic mental disorders and neurological diseases (e. g. dementia, epilepsy, stroke, multiple sclerosis)
6. Age < 18 years
7. Insufficient knowledge of the German language
8. Significant, not correctable impairment of hearing and/or vision
Additional exclusion criteria for study part 2
1. Cardiovascular or respiratory diseases (e. g. condition following a myocardial infarction, hypertension or hypertension requiring treatment, asthma, chronic obstructive pulmonary disease)
2. Neurodermatitis on the palms of the hands
3. Current severe hearing loss
4. Difficulty breathing during simple physical activities (e. g. walking)
5. Pregnancy
Additional exclusion criteria for study part 3
Standard MRI exclusion criteria (e. g. metallic implants)

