### Measures

#### Interviews and self-report measures (study part 1

Information on sociodemographic variables such as age, gender, relationship status, educational and occupational attainment, as well as anamnestic information on past and present medication, drug intake, and treatment is being collected through self-reporting.

The *primary outcome* is defined as the change score in the GSI (Global Severity Index) of the Brief Symptom Inventory (BSI) [130] measured during baseline (probatory phase) and between therapy sessions 20–24, or at the end of therapy if reached earlier. *Secondary Outcomes* and additional self-report questionnaires for basic research questions (baseline assessment) are presented in Table 2 [131–159]. Besides data collection before initiating therapy (probatory phase), primary and secondary outcomes will be collected again at sessions 20—24 and at each participant’s end of therapy. In addition to predictive questions, our project will also address other research questions (e.g., main effects of experiments and paradigms investigating transdiagnostic mechanisms and factors, and their association with psychopathology and transdiagnostic symptom dimensions).

**Table 2 Tab2:** Self-report questionnaires and therapist ratings

Measure	Description

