
### Challenges & limitations

Despite these various advantages, our study has also some challenges and limitations. As it is a naturalistic design, all eligible patients (and willing to participate in the study) seeking treatment at one of the outpatient clinics, are included. As a result of this approach, the distribution of specific disorders and the most frequent symptoms in the final sample are relatively unpredictable. This might for example lead to an overrepresentation of depressive disorders or symptoms, which we will however consider in our transdiagnostic analysis approach. In addition, the naturalistic setting precludes treatment according to standardized protocols and thus limits the validity of our findings. Another limitation is the absence of a waitlist control group, although the main question concerns the prediction of symptom reduction rather than the CBT effect. Nevertheless, any changes in symptom measures occurring during the study time period might also be related to factors and influences other than treatment alone. In addition, as symptom reduction at therapy sessions 20–24 is our primary outcome measure, it is not entirely clear how strong symptoms are already reduced at this point.

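### Inclusion criterion 3 depends on the course of therapy after baseline: it drops irregular early leavers from the baseline objective and can bias the prediction objective

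*Protocol article*

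**What the plan says.** Recruitment takes place before treatment (Study design and procedure): "During the probatory phase preceding psychotherapeutic treatment, patients are asked to participate in the TransTAM project". The abstract places marker collection at the same stage, with measures "ranging from basic perceptual processes and self-report measures to complex behavioral and neurobiological indicators, before entering therapy".

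Table 1 then lists, under the inclusion criteria for all participants, criterion 3: "Therapy duration of at least 12 sessions or a regular end of therapy before 12 therapy sessions must be reached".

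The primary outcome (Measures) is the change in the GSI of the Brief Symptom Inventory, "measured during baseline (probatory phase) and between therapy sessions 20–24, or at the end of therapy if reached earlier". The same section plans a further collection of primary and secondary outcomes at each participant's end of therapy.

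Objective 1 is "the association between transdiagnostic symptom dimensions and transdiagnostic factors and mechanisms"; the Discussion (Aim of the study) places it before psychotherapy. Objective 2 is "the prediction of symptom reduction from various transdiagnostic processes (and their relative importance) across emotional disorders". The abstract hopes to show "which patient groups with which symptom clusters are less likely to benefit from therapy, and for what reasons".

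The section on interpretation of data names selection through willingness and exclusion criteria, but not through early ending of therapy. The power section treats dropout only as a loss of patients.

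**The concern.** An eligibility criterion should be decidable when the patient enters. Criterion 3 is decided by what happens in the first 12 sessions, after consent and baseline testing. Below 12 sessions it sorts patients by how therapy ended: a regular end keeps the patient in, an irregular end takes the patient out. It is therefore not a pure minimum-exposure rule.

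Two things are at stake.

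- **Objective 1.** The association between markers and symptom dimensions before therapy does not depend on therapy length. Removing patients with complete baseline data costs precision and narrows the population for no evident gain.
- **Objective 2.** If irregular early ending is related to improvement, the retained sample is selected on the outcome. If it is also related to the marker, selection can create an association where none exists, or weaken or strengthen a real one. Because leavers become ineligible instead of having a missing outcome, the selection would not show up as missing data.

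**Working it through.** **1. The sequence in the text.** Recruitment and marker testing precede therapy. Criterion 3 can be judged at session 12 or at an earlier end, and the primary outcome falls at sessions 20–24 or an earlier end. So criterion 3 is a post-baseline condition for every patient. Nothing in the article keeps patients who fail it in any analysis.

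**2. The plan's own power figure.** The article claims 80% power for medium effects even with substantial dropout. The inputs are in Figure 1, which was not available, so exact reproduction is not possible. I assume f² = 0.15 and the overall F-test with noncentrality λ = f²·N at alpha 0.05:

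| Predictors | N for 80% power | Tolerable loss from 200 | Tolerable loss from 120 |
|---|---|---|---|
| 1 | 55 | 1 − 55/200 = 72.5% | 1 − 55/120 = 54% |
| 5 | 92 | 54% | 23% |
| 10 | 118 | 41% | 2% |

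The claim is plausible for part 1, and for parts 2 and 3 with few predictors. It does not address bias: enough patients can remain while the association shifts.

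**3. Possible size of the bias.** The text gives no drop-out rate and no relation of drop-out to marker or outcome, so everything here is assumed. The model has a standard normal marker X and improvement D. Irregular early ending follows logit(p) = c + a·X + b·D, with c set so that 10, 20 or 30% are excluded. There are 2,000,000 simulated patients per scenario. The true r is 0.36 (f² = 0.15 gives r = √(0.15/1.15) = 0.36) or 0.

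| Leaving depends on | r among retained, true 0.36 (10/20/30%) | r among retained, true 0 |
|---|---|---|
| Marker only (a = −0.7) | 0.35 / 0.35 / 0.35; slope unchanged at 0.36 | 0 |
| Improvement only (b = −1.0) | 0.35 / 0.34 / 0.34 | 0 |
| Both (a = −0.7, b = −1.0) | 0.31 / 0.28 / 0.26 | about −0.05 / −0.07 / −0.09 |
| Both, marker sign reversed (a = +0.7, b = −1.0) | 0.39 / 0.40 / 0.42 | about 0.05 / 0.07 / 0.09 |

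A second set used a true slope of 0.30, with odds ratios for leaving per SD of marker and of improvement:

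- Ratios 2 and 0.5 give slopes of 0.32 / 0.34 / 0.35.
- Ratios 0.5 and 0.5 give 0.26 / 0.23 / 0.22.
- The most extreme pair, 3 and 1/3, gives 0.35 / 0.37 / 0.40, and moves a null marker to 0.07 / 0.11 / 0.13.

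**4. Consequence for power in one bad case.** Take 120 patients less 30%, N = 84, one predictor: power is 94% at r = 0.36 and 67% at r = 0.255. The N of 84 already includes the lost patients. For part 1 under the same assumption, N = 200 × 0.7 = 140, power at r = 0.255 is 87%.

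**5. Does missing-at-random imputation repair it?** In the scenario where leaving depends on both (a = −0.7, b = −1.0), I set leavers' D to missing and imputed it from X. The slope was 0.305 / 0.272 / 0.250 after imputation, against 0.305 / 0.271 / 0.249 among those retained. Nothing is gained, because leaving depends on the unobserved improvement itself. Bias shrinks only if leavers supply a GSI, if other recorded variables explain the dependence, or if a missing-not-at-random assumption is examined.

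**The case against.** **A set with minimum exposure is a recognised choice** for predicting response to CBT actually received. That stands as a reason to report such a set, not as a reason to make it an entry condition. Criterion 3 is also not purely about exposure, since it keeps regular finishers with fewer than 12 sessions.

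**Many irregular leavers would have no follow-up GSI anyway.** This largely stands for objective 2. The article plans collection at each participant's end of therapy, but nothing shows that patients who break off will complete it. Part of the bias in the table may therefore be unavoidable missing outcome and not an effect of criterion 3. The argument does not touch objective 1.

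**The full protocol or analysis plan may keep the baseline data.** Possibly; the article does not say outright that they are discarded. But this is a stated eligibility rule, not an omitted detail, and it is listed for all participants.

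A reader might also infer more than the text supports:

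- That the limitations section contradicts Table 1 by saying "all eligible patients (and willing to participate in the study) seeking treatment at one of the outpatient clinics, are included". It does not: the word eligible refers back to Table 1.
- That the July 2024 counts (134, 78 and 27) conflict with criterion 3. They are counts of participation and do not claim that criterion 3 was met.
- That the excluded patients are those least likely to benefit. This is plausible but not documented.

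**Conclusion.** The wording defect is certain: criterion 3 conditions entry on post-baseline events and, as written, removes irregular early leavers from all study parts. The needless loss to objective 1 follows from that wording and rests on no simulation assumption.

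For objective 2 the conclusion is that associations can be biased, in either direction. To say that they are distorted would go beyond the documents. The slope is unbiased if leaving is unrelated to improvement given the marker. The bias is small if leaving depends on improvement alone (0.36 to 0.34 or 0.35). It reaches about 0.1 in r, or 0.13 in the most extreme case tried, when leaving depends strongly on both marker and improvement and up to 30% are excluded. All rates and dependences are assumptions.

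**What to change.** 1. Define eligibility by facts known at baseline. Turn criterion 3 into a completer analysis set, used for sensitivity analysis.
2. Objective 1: analyse every patient with a confirmed diagnosis and baseline data.
3. Objective 2: keep the same patients and use any end-of-therapy GSI already planned for each participant. Handle missing GSI with a mixed model or multiple imputation that includes baseline GSI, site and sessions attended.
4. Add a missing-not-at-random sensitivity analysis, for example delta adjustment: shift leavers' imputed improvement over a stated range and report when conclusions change.
5. Report irregular early ending against the markers, and name this selection in the limitations.
6. State whether the targets of 200 and 120 count patients before or after criterion 3.

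The cost is revised wording and some extra analysis, with no new assessments beyond those planned. The downside is that estimates for patients without follow-up rest on missing-data assumptions that the data cannot verify.
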